## Abstract

**Background:**

Tackling poor mental health in university students is a priority in higher education. Although major depressive disorder and generalized anxiety disorder are highly prevalent among university students and predict impaired university and later life outcomes, most students do not receive evidence-based treatment. Internet-delivered cognitive-behavioural therapy (iCBT) is increasingly offered to UK university students in guided or unguided formats. Our aim is to compare the effects of guided versus unguided scalable iCBT for university students with elevated symptoms of depression and/or anxiety and to investigate the feasibility of creating individual treatment rules (ITR) to predict for whom which variant of iCBT is more effective as well as for whom neither is effective.

**Methods:**

An online single-blind, two-arm parallel-group randomized controlled trial to examine symptoms of depression and anxiety across 3 months in university students aged over 16 who screen into the study with self-reported high levels of anxiety (GAD-7 > 9) and/or depression (PHQ-9 > 9). Eligible participants will be randomized to guided transdiagnostic iCBT supported by a psychological wellbeing practitioner or to the same transdiagnostic iCBT content as unguided self-help. In total, 720 participants with no current bipolar disorder or psychosis will be recruited from UK universities. Assessments will take place at baseline (pre-randomization) and 3 months post-randomization. Primary endpoints and outcomes are self-reported depression and anxiety symptoms at 3-month follow-up, adjusting for baseline scores. Well-being, health-related quality of life, functioning and academic outcomes are secondary outcomes. Compliance, adverse events, and potentially mediating variables will be monitored. We will use machine learning to estimate heterogeneity of treatment effects and develop an ITR to optimize the allocation of students to either unguided or guided iCBT.

**Discussion:**

The trial aims to provide a better understanding of the relative benefits of guided and unguided iCBT for anxiety and depression in university students with considerable implications for treatment coverage and service planning and delivery. We will provide innovative information to optimize treatment assignment, guide university mental health treatment planning and support evidence-based and scalable interventions for the most common mental health problems in university students.

**Trial registration:**

ISRCTN: 56784470, https://www.isrctn.com/ISRCTN56784470. Registered on 27 October 2022.

**Supplementary Information:**

The online version contains supplementary material available at 10.1186/s13063-025-09023-1.

## Background

Improving student mental health at university has increasingly been identified as a priority amongst both researchers [1–5] and key stakeholders [6–9]. Critically, there is increasing evidence of the high prevalence of anxiety and depression amongst university students globally [5, 10–12], with a series of international surveys finding that 25–40% of students report elevated anxiety and/or depression, often at a clinical level [4, 10–12].

In parallel, university mental health services report a dramatic increase in the number of students seeking help for mental health concerns and a growing disparity between student demand and current resources [5–9]. Since most United Kingdom (UK) students with mental health problems access services via their university rather than the National Health Service (NHS), there is now a major treatment gap. The organization, provision and means for students to access mental health services vary across institutions. None of the different service models nor most student mental health initiatives have been systematically evaluated and are often applied without a direct evidence base.

The recent UK University Mental Health Charter [8], a product of research synthesis, stakeholder consultation, and student co-creation, recommended a systemic whole-university approach to mental health, arguing that institutional environment, organizational culture, course content and delivery are all important for mental health, along with the integration of promotion and prevention and the provision of specialist support (see also 5,7). In parallel, recent reports [5] and the Universities UK StepChange framework [9] recommended stepped care tailored to the university environment to address the capacity and complexity of university mental health support needs. Stepped care typically involves access to and movement between different levels of intensity of intervention based on patient need and presentation [13].

One potential component within a stepped care model is the stepping up from through different intensities of therapy, with completely unguided self-help interventions such as unguided digital cognitive-behavioural therapy (CBT) offered for individuals with the mildest symptoms, the same digital CBT supported and guided by trained professionals, i.e. guided self-help, offered to individuals with mild-to-moderate symptoms, and with intensive face-to-face counselling or CBT offered to individuals with moderate-to-severe depression. Low-intensity (LI) self-help CBT, with or without support from a mental health professional, delivered via books or digitally is proven effective for treating common mental health difficulties [14–18], improves access and reduces delivery costs (e.g. the NHS Talking Therapies programme). Further, digital self-help is highly scalable and usable anywhere, anytime, potentially addressing treatment barriers and challenges around treatment access, capacity, convenience, and availability.

Digital CBT for mild-to-moderate anxiety and depression is found to be efficacious in students, albeit with small average effect sizes [19, 20]. However, most trials in students have only involved small samples (less than 100 participants per arm) and only a handful have selected participants with elevated anxiety and depression [21, 22]. Students generally view online interventions positively [23]. Despite this, self-help CBT has been less frequently evaluated within university student mental health support services, and when used, does not always adhere to established LI-CBT principles. There is an increasing use of digital CBT in UK universities as part of the portfolio of wellbeing services, often delivered in an unguided format, despite evidence that guided versions of CBT typically outperform unguided CBT interventions [17, 24, 25]. However, because co-morbidity of anxiety and depression is highly prevalent amongst university students, digital CBT interventions need to be sufficiently transdiagnostic to tackle both anxiety and depression, although most trials have focused separately on interventions for either anxiety or depression. To address these gaps, we plan the first large-scale trial in the UK of iCBT for students that will select students with elevated anxiety and/or depression scores, utilize transdiagnostic CBT, and compare guided versus unguided iCBT, relevant to improving stepped care approaches.

A key uncertainty within digital self-help is the heterogeneity of treatment effects; that is, variations in individual treatment response to different treatments [19, 24]. Understanding which digital self-help interventions are most acceptable and work best for which students could help to tailor self-help interventions, plan the care pathway, and improve outcomes. A critical question is how much and what kind of support from a practitioner is needed: unguided self-help has greater reach, sustainability and scalability as it is not limited by therapist capacity, opening up the potential for massive cost-effective open online interventions [26] but may have less engagement and efficacy than guided interventions [17, 20, 24, 25, 27, 28], although there is some heterogeneity [19, 24], with a subset of individuals benefiting as much from unguided self-help as guided self-help [25, 29]. Identifying such a subset would be of enormous value in increasing treatment scalability.

An emerging approach to develop precision predictive models is to use machine learning. A recent study used this approach to develop individualized treatment rules (ITR) for university students with anxiety or depression in Mexico and Colombia who had participated in a pragmatic trial comparing guided iCBT versus unguided iCBT versus treatment-as-usual [27, 30]. Machine learning enables the estimation of a prediction model for each treatment arm, which can then be used to determine counterfactual predicted outcomes for each student for guided i-CBT relative to unguided i-CBT and then to compare the difference between each predicted outcome to decide which treatment is best for each student. Such information could be very useful for deciding what type of treatment to offer different types of students and for planning of student treatment services.

Benjet et al. (2023) [30] used a machine learning precision treatment modelling method [31] to develop an ITR. We propose adopting a similar approach,thereby, to our knowledge, making the current study the first application of this approach to a European university student sample. This provides an opportunity to examine if similar patterns of heterogeneity of treatment effects and similar ITRs emerge in a UK higher setting compared to those found in Latin American higher education [27, 30]. Following the precedent of Benjet et al. (2023) [30], we will assess an extensive set of potential predictors of individual differences in the effects of CBT, that is, potential prescriptive predictors [32], moving beyond prior research that only examined a small battery of predictors [33]. As such, we aim to test whether it is possible to generate a useful ITR for guided versus unguided i-CBT in the UK university context.

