### Objective

The primary objective is to examine the aggregate efficacy of guided transdiagnostic i-CBT relative to unguided i-CBT to reduce symptoms of depression and anxiety over a 3-month period in university students who report elevated depression and/or anxiety, as operationalized by caseness on well-established self-report measures. As noted above, we know from much previous research that the aggregate efficacy of guided i-CBT is likely to be significantly higher than that of unguided i-CBT. A secondary objective is to use machine learning methods to predict heterogeneity of treatment effects of unguided iCBT versus guided iCBT and develop ITRs to predict which students will respond as well as, or possibly even better than, to self-guided as to guided i-CBT.

We hypothesize that consistent with prior findings [17, 20, 24, 25, 27, 28], for university students with elevated depression and/or anxiety, the guided i-CBT will outperform unguided i-CBT in the aggregate in reducing symptoms of depression and anxiety across 3 months. We further hypothesize that a small subset of users will benefit at least as much from unguided as from guided i-CBT and that we will be able to identify this subset of students prior to randomization using machine learning methods [30]. Importantly, we also anticipate that some proportion of students will fail to improve meaningfully with either guided or self-guided i-CBT and that we will be able to identify this segment of the population with good accuracy using the same machine learning measures as those used to develop the ITR. If so, this information could be used to refer such students to more intensive care rather than requiring them first to fail as a course of i-CBT.

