For the purposes of precision models, we will first explore which pre-treatment measures moderate the differential effects of treatment condition. Because individual predictors are usually weak and underpowered, our primary approach will be to use composite models that combine individual moderators to produce ITRs that can guide the selection of treatments most likely to be helpful for individual students. The approach will follow precedents established for developing precision treatment models via cross-validated machine learning methods as used in similar studies [30, 59–61]. Such machine learning methods for estimating heterogeneity of treatment effects include extensions of the generalized random forest algorithm [62–64] and of the Super Learner algorithm [65, 66], an ensemble machine learning approach. We will use the generalized random forest algorithm [62–64], with the option to add machine learning approaches (including ensemble approaches) as necessary, to develop a model that best predicts the relative effectiveness of alternative interventions. The machine learning approach has been validated for developing effective composite models, e.g. developing preliminary ITR with *n* = 150 [57, 61] and has the advantages of avoiding the need to specify main effects correctly and allowing the data‐driven estimation of nonlinear and higher‐order complex interactions across predictors. The value of guided and unguided iCBT at the individual level will be quantified using a counterfactual approach estimating the attained improvement of the mean outcome under a treatment selection scheme that always selects the treatment option with the best predicted outcome compared to the mean outcome under balanced randomization, generating a difference score or a personalized advantage index [67].

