## Discussion

There has been growing evidence for increasing prevalence of anxiety and depression amongst university students [1–5]. These common mental health problems are associated with lower academic grades and higher rates of drop-out from university as well as predicting negative impact on future careers. Critically, most students who experience anxiety and depression do not receive evidence-based interventions [6–10]. As such, there is an onus to determine scalable, feasible, and efficacious interventions and to appropriately direct students to the appropriate intervention.

Digital CBT provides one potential route to increasing coverage of efficacious interventions and is increasingly being offered as part of the portfolio of mental health services within UK universities, albeit often in an unguided format. It is therefore of great value to know the relative efficacy of guided versus unguided i-CBT for anxiety and depression in university students as well as to distinguish the subsets of students that are as responsive to self-guided as guided i-CBT, responsive only to guided i-CBT, and unresponsive to either and requiring further stepping up to higher intensity psychological therapy. Identifying an ITR is a key step towards precision treatment personalization and to prepare for definitive trials that test whether treatment allocation using ITRs improves outcomes relative to random allocation or usual practice.

The proposed comparison of guided vs unguided digital CBT is the most useful from a service delivery and cost-effectiveness perspective as it is the one with greatest implications for university wellbeing services implementation. Similar i-CBT packages are increasingly becoming a routine offer in UK universities, without knowing if they are being offered to the right students or if supported versions would do better if targeted appropriately. In the context of both increasing mental health demand in universities and constrained finances in higher education institutions, a better understanding of what works and for whom has considerable potential for impact in helping to develop more personalized and cost-effective services.

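### The learned treatment rule is valued only against balanced randomization, a yardstick that a rule no better than guided-for-all or a PHQ-9/GAD-7 rule can pass

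*Protocol article*

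**What the plan says.** The Background describes a stepped-care component that sorts by severity: "completely unguided self-help interventions such as unguided digital cognitive-behavioural therapy (CBT) offered for individuals with the mildest symptoms", then "guided self-help, offered to individuals with mild-to-moderate symptoms". These two levels correspond to the trial's two arms, and the same section says that the trial will "compare guided versus unguided iCBT, relevant to improving stepped care approaches". It closes with the aim for the rule: "we aim to test whether it is possible to generate a useful ITR for guided versus unguided i-CBT in the UK university context".

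The Objective section states the expected direction of the average effect: "the guided i-CBT will outperform unguided i-CBT in the aggregate in reducing symptoms of depression and anxiety across 3 months".

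The Statistical analysis plan section first explores single pre-treatment moderators and then builds a composite rule by cross-validated machine learning. The rule's value is the improvement in mean outcome under a scheme that "always selects the treatment option with the best predicted outcome compared to the mean outcome under balanced randomization". The article names no other comparator for the rule. The Discussion leaves it to later definitive trials to "test whether treatment allocation using ITRs improves outcomes relative to random allocation or usual practice".

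**The concern.** Balanced randomization gives half of the students the arm that is expected to be worse on average. A rule can therefore beat it simply by sending most students to guided iCBT, without knowing anything about who benefits. The yardstick mixes two sources of gain: the average advantage of guided support, and the information in the rule. Only the second bears on whether an ITR is useful.

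A service has two simple alternatives to a machine-learned rule. It can offer guided iCBT to everyone, or it can allocate on PHQ-9 and GAD-7, which every participant completes at screening. The learned rule draws on the extensive baseline battery. If it does no better than these alternatives, the planned index will not show it, and a positive index could be read as evidence of usefulness. The ITR is a secondary objective, but it raised the target from 129 to at least 300 per arm and is the reason for the long battery.

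**Working it through.** **No stated figure to reproduce.** The article gives no expected value for the rule, so the check concerns how the yardstick behaves.

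**1. What the yardstick rewards.** Let τ be a student's benefit from guided over unguided, D its mean, and A = 1 if the rule assigns guided. The gain over balanced randomization is V = E[τA] − 0.5·D.
- If a fraction q is assigned to guided at random, V = (q − 0.5)·D.
- At the article's PHQ-9 MCID, D = 2.59, and q = 0.8: V = 0.3 × 2.59 = 0.78 points, with no information used.
- Guided for all: V = 0.5 × 2.59 = 1.30 points.

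**2. A weak rule against a severity rule, in closed form.** Assumptions, not in the article: τ is normal with SD 1 to 2 PHQ-9 points, correlated 0.2 with the learned score and 0.3 to 0.6 with severity. The learned score is thus weaker by construction, so this shows what the yardstick lets through and not what is likely. Write s = correlation × SD.
- Half assigned to guided: V = 0.399·s. Learned: 0.399 × 0.2 = 0.08 to 0.399 × 0.4 = 0.16. Severity: 0.399 × 0.3 = 0.12 to 0.399 × 1.2 = 0.48.
- Each rule at its own cut-off: V = D·Φ(D/s) + s·φ(D/s) − D/2. At D = 0.5: learned 0.25 to 0.27, severity 0.26 to 0.52, guided for all 0.25.
- At D = 2.59 all three are 1.29 to 1.30.

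The weaker rule scores positive every time.

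**3. Simulation of the planned scheme, no quota on either arm.** Assumptions: 576 analysed (720 × 0.8, from the article's target and 20% attrition), 40 predictors including severity, mean benefit 0.25 SD, SD of effect modification 0.2, residual variance 0.7, ridge interaction learner. Entries are mean benefit kept (SD units) when severity drives none / half / all of the modification.

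| Rule | Benefit kept | Minus balanced randomization (0.125) |
|---|---|---|
| Learned rule | 0.230 / 0.230 / 0.231 | 0.105 / 0.105 / 0.106 |
| Severity only | 0.248 / 0.248 / 0.256 | 0.123 / 0.123 / 0.131 |
| Guided for all | 0.250 | 0.125 |

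In the first column of cases severity carries no information, yet the severity rule still scores +0.123. That is the defect of the yardstick, and it applies to any rule. The learned rule's shortfall against guided for all is 0.020 SD, or 0.020 × 5.4 = 0.11 PHQ-9 points.

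**4. Sensitivity.** Another run of the same set-up gave the learned rule 0.245 / 0.246 / 0.246 and severity 0.247 / 0.249 / 0.256, a gap of 0.002 to 0.010 SD (at most 0.010 × 5.4 = 0.05 points). The result turns on how strongly the ridge shrinks: heavier shrinkage moves the learned rule towards guided for all. The generalized random forest named in the plan was not simulated.

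**5. Power of an arm × severity interaction.** SE = 2·√0.7/√576 = 0.0697. At two-sided alpha 0.025 (Bonferroni for the co-primary outcomes), Φ(0.2/0.0697 − 2.241) = 0.73 if severity drives all of a modification SD of 0.2, and Φ(0.15/0.0697 − 2.241) = 0.46 at 0.15.

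**The case against.** The strongest reply is that the ITR work is a secondary, feasibility-stage aim. The abstract speaks of the feasibility of creating rules, and the Discussion defers comparison with usual practice to definitive trials. Single moderators are explored before the composite model, and depression and anxiety symptoms are among the candidate predictors, so severity is not ignored. Further benchmarks could sit in an analysis plan that is not shown.

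Part of this stands: nothing is wrong with the primary comparison, and the article sets no threshold for usefulness. But the article does name a yardstick, and the one it names cannot separate an informative rule from an uninformative one. Exploring moderators does not compare allocation rules, and including severity among the predictors does not guarantee that the composite beats a two-score rule out of sample. Allocation is randomized and baseline scores are collected, so the comparison can be made now.

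A reader might infer more, and three stronger readings are not supported:
- *Severity sorting is current or recommended practice that the rule must beat.* The Background calls it one potential component and says that delivery is often unguided. Entry at caseness or current major depression also removes most of the mildest students, and the article gives no unguided/guided cut-off within the sample.
- *The learned rule will do materially worse than severity sorting.* Differences of about 0.03 SD either way appear only when 30% of students are forced to unguided, which the planned scheme does not do. A ridge learner with independent predictors also cannot react to which predictor carries the signal.
- *The trial would recommend the long battery to services.* The text presents the ITR as preparation for further trials.

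**Conclusion.** The concern holds in limited form. The single stated yardstick can be passed by a rule that has little or no information or is worse than simple alternatives. For an uninformative rule this follows from the formula alone, whenever guided is better on average and more than half of students are sent to it.

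The size of any shortfall is uncertain. Under the simulation's assumptions the learned rule loses about 0.02 SD to guided for all while showing about +0.105 SD over balanced randomization; with other tuning the loss almost disappears. Guided for all is at least as necessary a benchmark as severity, because both simple rules converge on it when the average benefit is large. The primary efficacy analysis is unaffected. What is at stake is what may be concluded about a useful ITR.

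**What to change.** In the Statistical analysis plan section, keep the planned index and add two pre-specified benchmarks, evaluated in the same cross-validation folds as the learned rule:

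1. Guided for all.
2. A rule that uses only baseline PHQ-9 and GAD-7, compared with the learned rule both at each rule's own cut-off and at a matched share assigned to guided.

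Report the cross-validated paired difference in value (learned rule minus each benchmark) with a 95% interval. Base any statement that the ITR is useful on these contrasts and not on balanced randomization alone. A continuous arm × baseline severity interaction for each co-primary outcome may be added as supportive only, given its limited power. The benchmarks are analytic comparators and imply no rule for care.

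The cost is a few sentences of plan text and one small extra model on data already collected. The downside is that the headline ITR value may look smaller. Sample size and the primary comparison do not change.
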